## Abstract

**Background:**

Growing evidence links psychological well-being and resilience with superior cardiac health, but there remains a critical scientific gap about whether (or how) interventions that aim to cultivate psychological well-being reduce cardiac risk. Hispanic/Latino people in the United States have high cardiovascular disease risk and poorly controlled blood pressure (BP) compared with their peers of European ancestry, and they represent a population in need of new and innovative therapeutic approaches. As such, a focused intervention to boost psychological well-being holds promise as a novel therapeutic target for hypertension in Hispanic/Latino adults; to date, however, no research has explored whether a causal link is evident.

**Objective:**

The aim of this paper is to detail the protocol for the *¡Alégrate! (Be Happy!)* intervention, a Phase II randomized controlled trial testing initial efficacy in improving BP of a web-based positive psychological intervention designed to boost psychological well-being in Spanish-speaking Hispanic/Latino people with hypertension.

**Methods:**

A total of 70 Hispanic/Latino people aged ≥18 years, fluent in Spanish, and with elevated BP (≥140/90 mm Hg) will be recruited in person from a single Federally Qualified Health Center in Chicago. Enrollees will be randomly assigned to 1 of 2 trial arms: (1) web-based positive psychological intervention or (2) an active control condition (eg, 3 times weekly emotion reporting). Our 5-week Spanish-language *¡Alégrate!* intervention is web-based and delivers curricular content via didactic instruction, journaling, and assigned at-home practice—all accessed via our website using investigator-purchased tablet computers, with a unique username and password assigned to each enrollee. Targeted skills include noting daily positive events, positive reappraisal of stressful events, effective expression of gratitude, performing acts of kindness, and regular practice of mindfulness and meditation. The primary outcome is improvement in BP, both sitting values and 24-hour ambulatory readings, as measured at baseline and 5 and 12 weeks from baseline. Secondary outcomes include psychological well-being, engagement in healthy behaviors, and circulating levels of inflammatory markers. The outcomes of interest are collected by trained research staff through in-person interviews using the REDCap software.

**Results:**

Activities of the *¡Alégrate!* intervention were funded in August 2017, and data collection is ongoing. We expect to submit trial results for peer-reviewed publications in 2021, soon after recruitment has been concluded and statistical analyses are finalized.

**Conclusions:**

Findings will provide evidence on whether interventions to boost psychological well-being and resilience have downstream effects on BP control and cardiovascular health, particularly as they are deployed in the Spanish language with cultural tailoring and via a web-based platform. If effective, we will have an easily disseminatable application that can positively impact well-being profiles and BP control in Hispanic/Latino people, with the possibility of addressing health disparities of this US racial/ethnic minority group.

**Trial Registration:**

ClinicalTrials.gov NCT03892057; https://clinicaltrials.gov/ct2/show/NCT03892057

**International Registered Report Identifier (IRRID):**

PRR1-10.2196/17721

## Introduction

One in every 3 adults in the United States is classified as hypertensive and only around half maintain blood pressure (BP) under control [1-3]. Cardiovascular disease (CVD) is the leading cause of death in the United States, and hypertension exhibits the highest attributable risk for CVD morbidity and mortality [4]. Mounting evidence suggests that positive psychological well-being (hereafter, psychological well-being)—which includes positively valenced feelings or cognitive appraisals such as happiness, optimism, and purpose in life—is independently associated with favorable cardiac health, for example, reduced risk for incident hypertension, better lipid profiles, reduced inflammatory markers, and reduced odds of incident heart disease and cardiac-related mortality [5-7]. Nevertheless, while multiple studies link psychological well-being with better cardiac health [6-8], there is a need to investigate the most effective approaches to cultivate psychological well-being in an effort to reduce cardiac risk.

While scholars define psychological well-being in various ways [9,10], in the field of cardiovascular epidemiology, it encompasses positively valenced feelings or cognitive appraisals that individuals use to evaluate their lives favorably [7,8]. As such, 2 theoretical perspectives inform the characterization of psychological well-being: the hedonic approach, which focuses on pursuit and attainment of pleasure and happiness [11], and the eudaimonic approach, which defines well-being as the ability to practice meaningful life pursuits and striving to realize one’s best self [11]. Other domains, which are less easily classified as hedonic versus eudaimonic (eg, optimism, emotional vitality), have consistently predicted cardiovascular outcomes. Common measures of psychological well-being include purpose in life, personal growth, self-acceptance, environmental mastery, autonomy, happiness, satisfaction in life, positive affect, optimism (and hope), and emotional vitality.

The Hispanic/Latino population in the United States is a racial/ethnic group that may benefit from novel treatment focused on improving psychological well-being [12]. There are 57 million [13] Hispanic/Latino people in the United States, and they represent the second fastest growing ethnic/racial minority group [14,15]. Hispanic/Latino people exhibit a disproportionately higher burden of cardiovascular disease risk factors [3,16]. In addition, the Hispanic/Latino population has a higher incidence rate for CVD-related comorbidities (eg, chronic kidney disease) when compared with non-Hispanic populations, with 30% mortality attributable to CVD and its sequelae [14,17,18]. Additional research is needed, however, to explore strategies that boost psychological well-being specifically in Hispanic/Latino adults and whether this leads to better heart health and BP management. To date, pilot trials highlight that Hispanic/Latino adults find interventions targeting psychological well-being both enjoyable and beneficial [19,20].

Observational evidence links psychological well-being with better overall health, more healthy coping tendencies, improved quality of life, and healthy longevity [8,21]. Psychological well-being focuses on positive thoughts and feelings at the individual level, which may be key in promoting healthy behaviors in hypertension management [8]. Evidence suggests that psychological well-being is related to healthier BP profiles and plays a protective role in disease incidence [7,22]. In over 1000 healthy non-Hispanic adults, a large prospective study found that higher levels of psychological well-being were associated with a decreased likelihood of incident hypertension at a one-year follow-up [23]. In 126 British civil servants, aggregate baseline levels of happiness were negatively associated with 3-year measures of systolic BP, independent of known confounders.

Approximately 22% [15] of Hispanic/Latino people have hypertension, and they tend to display lower compliance with treatment recommendations when compared with their non-Hispanic peers [15,17]. Adherence to antihypertensive treatment and effective BP control in Hispanic/Latino people was approximately 58% and 35%, respectively, compared with whites (71% and 48%, respectively) and blacks (71% and 43%, respectively) [24]. There are no specific clinical CVD guidelines addressing the unique characteristics of Hispanic/Latino people, which highlights the need for novel and more effective disease management efforts for this racial/ethnic group [14].

The use of web-based interventions in different clinical populations has grown significantly [25]. Web-based interventions tend to be less costly than face-to-face designs, offering flexibility and greater access [26]. Internet use has also grown substantially among Hispanic/Latino adults, with 80% reporting use of the internet [26]. A majority of Hispanic/Latino people reported having a computer (78%) and reported owning a smartphone (71%) [27]. Web-based interventions have the potential for broad dissemination and may help eliminate common barriers to participation (eg, transportation, scheduling conflict, and lack of child care) [28]. Recent studies have used web-based interventions to promote psychological well-being in different patient populations [25]. For example, web-based delivery formats were found to be effective in the management of symptoms of depression, anxiety, and stress [29-33] in healthy and clinical populations. However, most of these studies have been conducted on non-Hispanic white samples. There is a need for better representation of underserved, racial/ethnic minorities in web-based psychological well-being interventions.

Empirical evidence suggests that effect sizes for web-based therapies are similar to those deployed using traditional face-to-face approaches, with high patient satisfaction reported across these high-tech platforms. Few evidence-based programs, however, have been developed specifically for and deployed with Hispanic/Latino adults using web-based platforms. Schueller et al [34] identified only 6 studies that deployed digital health technologies in Hispanic/Latino populations. Given the paucity of evidence, testing for feasibility is imperative to document whether insurmountable barriers are evident, for example, limited internet accessibility and low technology literacy, among others. For instance, in past years, Hispanic/Latino adults have reported low Wi-Fi accessibility when compared with their peers of European ancestry, but important strides have been made in recent years with 81% of Hispanic/Latino adults now reporting internet access—although, usually in the form of mobile-only internet access versus at-home networks. Nonetheless, with increased accessibility, web-based platforms can become viable avenues because of their low cost and potential for broad dissemination, particularly among marginalized, underserved, and minority populations that encounter multiple barriers in accessing care, such as lack of health insurance or shortage of Spanish-speaking clinicians. Indeed, the use of technology represents a promising opportunity as Hispanic/Latino people express high interest (ie, ~86%) in engaging health-related phone apps and related technologies [34].

*¡Alégrate! (Be Happy!)* is a Phase II randomized controlled trial (RCT) created to address these limitations by testing the initial efficacy of a Spanish language web-based intervention. The RCT intends to boost psychological well-being in Spanish-speaking Hispanic/Latino adults with hypertension by examining changes in BP, psychological well-being, healthy behavior adherence, and circulating serum inflammation. This web-based intervention is built on activities that target psychological well-being by promoting optimism, gratitude, and positive affect directly through activities such as recalling positive life events, identifying and employing personal strengths, and engaging in acts of kindness, among others. We hypothesized that compared with participants in the control condition, those in the active intervention group will show greater improvements in BP, higher scores for psychological well-being, greater engagement in healthy behaviors, and lower levels of inflammatory markers at follow-up. The aim of this paper was to detail the procedures of the ¡Alégrate! Phase II trial: Focus on the design and protocol of the web-based intervention.

## Methods

### Overview and Study Design

This study, known as *¡Alégrate! (Be Happy!)*, is an RCT testing the initial efficacy of a 5-week web-based positive psychological intervention in Spanish-speaking Hispanic/Latino adults with hypertension. As such, the current Phase II pilot trial implements a parallel group design with a 1:1 allocation ratio, with 2 fixed factors: (1) sex (male and female) and (2) antihypertensive medication use (yes and no). Participants assigned to the treatment condition will be asked to visit the *¡Alégrate!* study website over a 5-week period in which they learn skills known to boost positive emotion and overall psychological well-being, while participants in the active control condition engage in emotion reporting 3 times weekly. Participants assigned to the active control condition will gain access to the web-based curriculum at the end of the 12-week assessment period, after all survey and clinical data has been collected.

### Participant Eligibility

Spanish-speaking Hispanic/Latino adults are eligible to enroll in the *¡Alégrate!* trial if they meet the following criteria: (1) Hispanic/Latino heritage based on self-report; (2) aged 18 years or older; (3) fluent in Spanish, that is, ability to read, speak, and write Spanish; (4) elevated sitting BP (≥140/90 mm Hg); and (5) basic technological literacy with the ability to access the internet at home or in a public setting. The exclusion criteria were as follows: (1) cognitive impairment denoting dementia [35], (2) severely reduced life expectancy (eg, self-reported diagnosis of metastatic cancer, congestive heart failure, or end-stage kidney disease), and (3) severe psychopathology including active psychosis or untreated bipolar disorder. The Institutional Review Board at the University of Illinois at Urbana-Champaign (UIUC) approved the *¡Alégrate!* trial, and all subjects provided written informed consent.

### Study Procedures

#### Recruitment

Participants were recruited from a single Federally Qualified Health Center (FQHC) located in Chicago and situated in a neighborhood with a high density of Hispanic/Latino residents. The attending physician and clinical staff (eg, registered nurse, medical assistant) identify potentially eligible patients and subsequently refer them to *¡Alégrate!* research staff who then follow-up via phone or in person; participant information is stored in a secure web-based portal. During phone or in-person exchanges, the staff inform participants that the goal of the study is to explore whether an intervention intended to boost positive emotions results in better cardiac-related health. Only initial eligibility is determined via phone, with an in-person visit scheduled to establish full eligibility based on sitting B*P* values. Research staff will also approach patients in the waiting area to provide information about the research study and offer an invitation to receive a no-cost BP screening; research staff will collect contact information of those expressing interest to determine full eligibility. The consent form and study materials outline the design of the study and inform participants of random assignment into 1 of 2 groups, either the group where *they learn skills known* to *boost mood and heighten positive emotions* or the group where *they would report experiences of positive or negative emotions on a thrice weekly basis*. It is communicated that all curricular instruction occurs online by visiting our *¡Alégrate!* website. In addition, the staff inform participants that 3 in-person clinical visits are required, each 2 to 3 hours in length, where staff collect survey and clinical data including anthropometric information, blood spots, and 24-hour BP monitoring; home visits are also offered for data collection to increase rates of retention. Participants are informed that they can keep the investigator-purchased tablet computer at the end of the study as compensation for their participation and time invested [36]. To reduce the risk of bias, enrollees in both the treatment and control arms keep the tablet computer at the end of study participation, that is, immediately after providing follow-up survey and clinical data at 12 weeks postbaseline. Participants expressing interest in enrolling in the trial who are screened for full eligibility and ultimately qualify undergo a face-to-face consent process and complete the survey and clinical exams before randomization.

#### Consent, Assessments, and Randomization

Survey and clinical exams occur in tandem at 3 time points, as follows: Time 1 (baseline) at study enrollment; Time 2, immediately postintervention (5 weeks after baseline); and Time 3 (12 weeks after baseline). Figure 1 details the design of the study and the associated timeline for recruitment, enrollment, and assessment tasks.

Survey and clinical assessments are conducted in Spanish through in-person interviews by trained bilingual research staff in a one-to-one encounter at the participating FQHC. Questionnaires used and associated constructs assessed as part of the survey interview includes measures of psychological well-being (eg, optimism, positive affect), acculturation, self-reported health and medical comorbidities, engagement in healthy behaviors (eg, sodium intake, sleep quality, and duration), and medication adherence. Many survey instruments used in the current trial have undergone previous psychometric testing, showing adequate validity and reliability in the Spanish language. For those not previously translated, our team conducted thorough forward and backward translation procedures to craft a Spanish-language adaptation with linguistic equivalency. All survey data were collected using REDCap, a secure internet-based platform for building and managing web-based surveys. Finally, clinical examinations will be carried out by research staff to collect anthropometric data (eg, body mass index, waist-to-hip ratio), serum blood spots, sitting BP, and 24-hour ambulatory BP profiles. It should be noted that all data will be deidentified, stored in a password-protected computer, and/or stored in a locked cabinet in the principal investigator’s office.

After determining full eligibility, participants will be enrolled in the trial by providing written informed consent. After completing baseline assessments, participants will be randomly assigned in a 1:1 ratio to the intervention or active control condition using block randomization alternating between varying block sizes of 4, 6, or 8. The principal investigator created a random allocation table using Sealed Envelope, after which it was uploaded to REDCap to define the randomization model of *¡Alégrate!* to ensure proper blocking and stratification by sex (male and female) and use of antihypertensive medication (yes and no). A trained research staff generated allocation assignment through REDCap. It should be noted that REDCap conceals the allocation table and associated sequencing from research staff to prevent selection bias. Finally, given the pilot nature of a Phase II trial, blinding occurs only at the level of data analysis.

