### Planned Analyses

The primary outcome of the *¡Alégrate!* trial focused on prospective changes in B*P* values, that is, both sitting BP and 24-hour ambulatory readings. The first aim was to examine the efficacy of the intervention in reducing B*P* values immediately postintervention (ie, 5 weeks) and at the 12-week follow-up period, that is, Exams 2 and 3. The second aim was to explore whether the intervention leads to significant improvements in psychological well-being and greater adherence to healthy behavioral practices. We will additionally test whether psychological well-being and healthy behaviors serve as mediators when exploring intervention effects on BP control. The third aim is to test intervention effects on circulating markers of inflammation, specifically high-sensitivity C-reactive protein.

Descriptive statistics, at baseline, will summarize participant characteristics for the full sample and stratified by intervention arm. Bivariate tests will be conducted to compare the intervention and control conditions to ensure compatibility across key variables (eg, demographic factors, well-being profiles, etc) and to test the success of the randomization protocol. Discrepancies in baseline values across conditions will inform covariates for inclusion when testing our main hypotheses of interest. In addition, we will document the number of missing observations over time to assess the potential for bias resulting from significant dropout and differential attrition by condition. We will perform independent sample two-tailed *t* tests and/or Fisher exact tests to compare baseline characteristics of enrollees who completed the trial versus those who prematurely dropped out, allowing us to test possible predictors of attrition.

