Given our design and main objective of treatment evaluation, an intent-to-treat analysis will be conducted, where we will consider the data of all participants randomized, with retention of their original intervention assignment. Sensitivity analysis will use multiple imputation procedures across missing values to ensure inclusion of all observations, particularly those resulting from participants who withdraw, are lost to follow-up, or do not complete all assessments. In a supplementary analysis, we will use ordinary or logistic regression (as appropriate, given variable distribution) to implement a dose-response analysis to test whether participation-related factors (eg, number of sessions viewed, rate of homework completion) impact outcomes of interest.

We estimated the sample size requirements of a two-arm randomized trial to evaluate whether our web-based positive psychological intervention resulted in differential and clinically meaningful improvements in systolic BP of 6 mm Hg compared with an attention control condition. A repeated-measures design with systolic BP determination at baseline and 5 and 12 weeks was used. In addition, the following operating characteristics were assumed: (1) a between-subject standard deviation for BP of *σ=12 mm Hg*; (2) a within-subject correlation, *ρ=0.60* (3) a two-sided type I error probability of 0.05; and (4) 80% statistical power. Frison and Pocock [65] argue that adjusting for baseline measures (analysis of covariance) results in a more efficient analysis for a given sample size (larger statistical power). This approach yields an estimate of the required sample size of 28 participants per study arm under equal allocation. Furthermore, assuming a conservative attrition rate of 20%, an updated estimation produces the following sample size of participants per study arm.

[figure not shown]

Stata 15 was used for sample size calculation (*sampsi* command) and all statistical analyses, with effect size estimation derived from published data on the clinical effectiveness of psychotherapeutic interventions to treat hypertension [47,66,67].

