#### Aim 1: Determine the Efficacy of the ¡Alégrate! Web-Based Positive Psychological Intervention in Improving BP Control in Hispanic/Latino People With Hypertension From Baseline, Immediately Postintervention (5 Weeks), and at 12 Weeks After Baseline 

Independent samples *t* tests will be performed using 5-week systolic BP and diastolic BP as the dependent variables, with treatment condition serving as the grouping variable. Other model-based approaches to handle missing data, such as weighted estimating equations, will be implemented. We will also use mixed-effects models to compare changes in BP between the control and intervention arms as measured at baseline, 5 weeks, and 12 weeks. The independent variables include a time variable t (t=0, 5, 12), a dummy variable N (N=1, if PP intervention group; N=0, if attention control), and a cross-product term (t×N). For ambulatory data collected across a 24-hour period, sensitivity analyses will compare mean overall daytime versus nighttime values of BP. All data analyses were conducted using SAS 9.4 software (SAS Institute).

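### Randomisation is stratified by sex and antihypertensive use, but the 5-week t test leaves both out, which makes that test somewhat conservative if the factors predict blood pressure

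*Protocol article*

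**What the plan says.** Overview and Study Design describes a parallel-group trial "with 2 fixed factors: (1) sex (male and female) and (2) antihypertensive medication use (yes and no". Consent, Assessments, and Randomization says that participants are "randomly assigned in a 1:1 ratio to the intervention or active control condition using block randomization alternating between varying block sizes of 4, 6, or" (the third block size is 8), and that the allocation table was loaded into REDCap "to ensure proper blocking and stratification by sex (male and female) and use of antihypertensive medication (yes and no".

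Aim 1 then names two analyses of blood pressure:

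- At 5 weeks, a two-sample t comparison: "tests will be performed using 5-week systolic BP and diastolic BP as the dependent variables, with treatment condition serving as the grouping variable".
- Over baseline, 5 and 12 weeks, a mixed-effects model: "The independent variables include a time variable t (t=0, 5, 12), a dummy variable N" for treatment, and their product.

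Neither mentions sex or medication use. Aims 2 and 3 refer back to similar techniques and test the group-by-time interaction. The only general rule on covariates is in Planned Analyses: "Discrepancies in baseline values across conditions will inform covariates for inclusion when testing our main hypotheses of interest".

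**The concern.** Blocking within the four sex-by-medication strata keeps the arms nearly balanced on both factors, so differences between strata contribute little to the true variability of the treatment contrast. A two-sample t test does not know this. It leaves the between-stratum variation in its error term and reports a standard error that is too large wherever the factors predict the outcome. The precision that stratification bought is then not used.

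The covariate rule does not close the gap. It selects variables that differ between arms at baseline, and stratified blocking is meant to prevent such differences for these two. A two-sample t test has no place for a covariate in any case.

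At stake is some power in a trial of 70 people, not the validity of a positive result.

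**Working it through.** **Inputs from the article.** Planned Analyses: difference 6 mm Hg systolic, SD 12 mm Hg, within-subject correlation 0.60, two-sided 5%, 80% power, 28 per arm, 20% attrition. Abstract: 70 in total. Randomisation: 1:1, blocks of 4, 6 or 8, four strata.

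**Assumed.** The article gives no share of 5-week variance explained by the strata. Call it r, with a range of 5 to 20%. The simulations take splits of 60/40 and 70/30 for the two factors.

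**1. The plan's own figure.** For an analysis of covariance with one baseline and two follow-ups:

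n = 2 × (1.96 + 0.84)² × 12²/6² × [(1 + 0.60)/2 − 0.60²] = 62.79 × 0.44 = 27.63, so 28 per arm.

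28/0.80 = 35 per arm, or 70 in total. Both figures reproduce.

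**2. Closed form for the 5-week t test.** With perfect balance within strata, true SE = √(1 − r) × reported SE. The reported SE is therefore too wide by the factor 1/√(1 − r), and the actual two-sided error is 2[1 − Φ(1.96/√(1 − r))].

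| r | SE too wide by | Actual type I error |
|---|---|---|
| 5% | 2.6% | 4.4% |
| 10% | 5.4% | 3.9% |
| 20% | 11.8% | 2.8% |

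**3. Simulation with the stated blocks.** Incomplete blocks leave some imbalance, so the closed form is an upper bound. N = 70, no dropout, 8,000 null and 4,000 alternative trials per scenario:

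| r | Reported SE, t test | True SD of estimate | SE too wide by | Type I, t test | Type I, strata added | Power at 6 mm Hg, t test | Power, strata added |
|---|---|---|---|---|---|---|---|
| 0% | 2.86 | 2.88 | none | 5.2% | 5.3% | 54% | 54% |
| 5% | 2.86 | 2.79 | 2.5% | 4.5% | 4.8% | 55% | 57% |
| 10% | 2.86 | 2.77 | 3.2% | 4.3% | 5.4% | 55% | 59% |
| 20% | 2.86 | 2.57 | 11.3% | 2.9% | 4.7% | 56% | 65% |

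The simulation error on the type I rates is about 0.2 percentage points. A separate run gave 4.0% and 3.2% for the t test at r = 10% and 20%, and power rising from about 55% to 60–63%. With 20% dropout, the t test's type I error was 4.5%, 4.3% and 3.5% at r = 5, 10 and 20%.

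**4. What the strata add once baseline blood pressure is in the model.** Suppose the stratum effect is the same at both visits. Residual variance with baseline alone is 1 − 0.60² = 0.64. With the strata added, the within-stratum correlation is (0.60 − r)/(1 − r).

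- r = 5%: 0.95 × [1 − (0.55/0.95)²] = 0.632; √(0.64/0.632) is about 1.007.
- r = 10%: 0.90 × [1 − (0.50/0.90)²] = 0.622; √(0.64/0.622) is about 1.014.
- r = 20%: 0.80 × [1 − (0.40/0.80)²] = 0.600; √(0.64/0.600) is about 1.033.

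The further gain is thus about 1 to 3% in SE.

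**5. Mixed-model treatment-by-time term.** A random subject intercept is assumed; r = 20%; 150 simulated trials per scenario.

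- Complete data: the same estimate and an SE of 0.2115 with or without the strata.
- 20% of follow-up visits missing: 0.2320 without the strata, 0.2313 with them.
- Assumed medication-by-time slope of 0.5 mm Hg per week: 0.2153 without the strata, 0.2119 with stratum-by-time terms, about 1.6% apart.

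**The case against.** The text is less closed than it looks. The mixed-model list says what the variables include, the design statement calls sex and medication use fixed factors, and Table 2 has sex among the demographic covariates. A condensed article may leave the full covariate list to an analysis plan that is not shown. This has weight for the mixed model. It does not rescue the 5-week comparison, where the article names a test that cannot carry a covariate. Table 2 also places medication use under the secondary outcomes, not the covariates.

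The size is assumed. If the strata do not predict blood pressure, nothing is lost, and at r of 5% or less the effect is hardly visible. This stands.

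Most of the recoverable precision comes from baseline blood pressure, not from the strata. This also stands. The sample size assumes a baseline-adjusted analysis, and the gap between that and an unadjusted t test is a separate and larger matter that should not be counted towards this point.

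A reader might infer that all the planned models give standard errors that are too wide. Step 5 does not support that: the subject intercept absorbs a stable stratum effect, so the treatment-by-time contrast, and with it the group-by-time tests in Aims 2 and 3, hardly changes.

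**Conclusion.** The point holds for the 5-week t test under Aim 1, at low severity. The design stratifies on two factors, the named test ignores them, and the imbalance-driven rule would normally leave them out.

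If the strata explain 5 to 10% of 5-week variance, the t test's standard error is about 3 to 5% too wide and its type I error is about 4 to 4.5%. At 20%, these become about 11 to 12% and about 3%. All of this rests on the assumed range for r, since the documents give none.

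A reader might take a test that is not at its stated 5% to mean excess false positives. The departure is in the other direction: the error is below 5%, the cost is power, and the validity of a positive finding is not in question.

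**What to change.** Replace the 5-week t test with a linear model (analysis of covariance) that contains treatment, the baseline value of the outcome, sex and baseline antihypertensive use. State that the two strata enter whatever the observed balance. Take medication use from the randomisation record, because it is also measured again at later visits as an outcome.

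Carry the strata into the mixed models of Aims 1 to 3 so that the analysis matches the design, without claiming a gain in precision there.

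The cost is 2 degrees of freedom for the strata. Both factors are already held in REDCap, so no new data are needed.
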